## Abstract

**Background:**

The positive impact of fundamental movement skills on physical activity in young children has been shown in previous studies, but little is known about the association between fundamental movement skills and cognitive development in young children. This study protocol describes a 10-month, four-arm cluster randomized crossover trial evaluating the effectiveness of the “Advancing Movement and Physical Literacy Earlier” (AMPLE) program in promoting physical literacy and executive function among 3-5-year-old children in 18 Hong Kong kindergartens.

**Methods:**

This program integrates fundamental movement skills training with cognitively challenging activities. Four classes per kindergarten will be randomly assigned to one of four conditions: (1) combined fundamental movement skills and cognitive challenge, (2) sedentary with cognitive challenge, (3) fundamental movement skills alone, or (4) sedentary without cognitive challenges. Each condition involves 30-minute sessions, three times per week, with a six-week washout period between the three-week intervention phases. The research team will use multiple objective measures and self-report measures, covering the elements and domains of the assessment of physical literacy and executive function. Three follow-up tests will be conducted within six months after the end of the intervention to evaluate the long-term impact of the program. Intervention implementation and fidelity will be assessed through focus group interviews with teachers and principals.

**Discussion:**

The “AMPLE” program aims to strengthen the theoretical understanding of motor‒cognitive connections, inform early childhood education practices, and contribute to public health strategies promoting lifelong physical activity. Ultimately, the program seeks to provide evidence-based interventions for fostering holistic child development and establishing healthy lifestyle habits.

**Trial registration:**

The protocol has been registered at Chinese Clinical Trial Registry on August 27, 2025, under identifier ChiCTR2500108295.

**Supplementary Information:**

The online version contains supplementary material available at 10.1186/s12889-025-25753-y.

## Background

Early childhood is the opportune time to promote regular physical activity (PA) engagement and cognitive development, which are crucial for reducing the likelihood of obesity and disease and establishing a foundation for academic achievement [1–4]. As a component of complex movement sequences and sport participation [5, 6], there is increasing evidence that interventions based on Fundamental Movement Skills (FMS) are positively correlated with children’s cognitive function development, especially in terms of memory enhancement [7, 8]. Some perspectives also point out that FMS with cognitive engagement may have better intervention outcomes than single PA/FMS engagement does [9, 10]. One possible mechanism is that FMS allows for the activation of neural networks, and a more aroused neural network state contributes to performance when performing cognitive activities, whereas cognitively integrated FMS tasks activate neural networks for complex cognitive tasks, which allows for higher levels of cognition to be trained [11–13].

However, current research on FMS/PA-based executive function (EF) interventions generally suffers from poor methodological quality, with some studies failing to use validated or reliable assessment methods to examine cognitive functions [8]. Moreover, there have been few interventions or assessments for preschoolers, and some studies have addressed only the relationship between FMS and PA participation in preschoolers without considering possible cognitive effects [14, 15]. There are also some studies whose findings are inconsistent with the hypotheses, and this difference deserves to be explored further [16]. For example, studies have shown no benefit of PA engagement on executive function [17–19] and possibly even negative effects [20]. Possible reasons for these discrepancies include insufficient intensity of the cognitive challenges, fatigue from excessive PA intensity, or a loss of positive emotions [18]. EF develops most rapidly between the ages of 5–8 years, so young children may be more sensitive to these issues, and these possible issues pose a challenge for future research.

As more interventional studies have been conducted, a considerable degree of limitation has emerged from purely quantitative studies. Controlling for the intensity or duration of PA interventions alone, for example, does not seem to lead to a uniform conclusion that not all exercise interventions demonstrate a good ability to improve cognitive functioning [21]. As a result, researchers have gradually turned their attention to qualitative characteristics of how to develop more effective PA intervention models while harmonizing cognitive and motor abilities and why some interventions have a greater ability to improve cognitive function than others do [22]. We should assume that not all PA-related interventions can have a significant positive impact but rather need to consider elements such as the quality of intervention and the measurements used for cognitive development that are critical in influencing intervention outcomes [23].

While PA itself is undeniably important, the emerging concept of physical literacy (PL) offers a more comprehensive and promising approach to cultivating positive movement behaviors and maximizing the benefits of PA across the lifespan [24, 25]. PL emphasizes the development of not only physical competence but also the motivation, confidence, knowledge, and understanding needed to value and take responsibility for engagement in physical activities for life [26]. This broader perspective, which acknowledges the interconnectedness of physical, cognitive, affective, and social domains in shaping an individual’s relationship with movement and activity, is helpful for guiding effective strategies to improve the quality of early intervention for promoting PA [27]. Research has shown that taking specific measures to improve the PL of specific populations is effective, but the mechanism is unclear [28–30], and education programs specifically designed for PL assessment are still lacking [31].

The need for effective intervention is particularly acute in Hong Kong, where studies indicate that a significant majority of preschoolers fail to meet recommended physical activity (PA) guidelines from the World Health Organization, leading to a downward trend in their Fundamental Movement Skills (FMS) [32, 33]. The problem is compounded by the lack of a standardized physical education curriculum in Hong Kong kindergartens, creating a significant gap in our understanding of local children’s FMS and EF levels [34].

In response to these challenges, a growing body of evidence supports the idea that FMS interventions integrating cognitive engagement from the perspective of PL may be more effective than single PA/FMS interventions in terms of physical and cognitive outcomes [8]. Such strategies are capable of significantly enhancing young children’s physical outcomes while simultaneously improving their cognitive development [35, 36]. This study introduces the “Advancing Movement and Physical Literacy Earlier” (AMPLE) program, a cluster randomized crossover trial (CRXO) designed to enhance both PL and EF in Hong Kong preschoolers. AMPLE uses an approach that integrates FMS development with cognitively challenging activities. This integrated approach aims to capitalize on the synergistic relationship between motor and cognitive development, maximizing the potential for holistic child development. By targeting both FMS and EF, the AMPLE program aims to not only increase PL and PA participation and improve physical health but also enhance cognitive function, contributing to long-term population and social well-being. This study provides valuable insights into the effectiveness of this integrated approach and contributes to the development of evidence-based interventions for promoting PL, PA and cognitive function in young children. Specifically, the research questions of this study are as follows: (a) What are the effects of the intervention on children’s physical literacy and executive function compared with usual care? (b) What factors may influence the effectiveness and fidelity of the intervention? We hypothesize the following after the intervention and follow-up:H1. The participants in the intervention groups will experience greater increases in cardiorespiratory fitness and FMS than their counterparts in the control group, with the greatest improvement in the combination group.H2. The participants in the intervention group will experience greater increases in executive function than their counterparts in the control group, with the greatest improvement in the combination group.H3. The participants in the intervention group will experience greater increases in affective competence than their counterparts in the control group, with the greatest improvement in the combination group.H4. The participants in the intervention group will experience greater increases in social competence than their counterparts in the control group, with the greatest improvement in the combination group.H5. The participants in the intervention group will experience greater increases in PA participation levels than their counterparts in the control group, with the greatest improvement in the combination group.

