### Participants

The study will include typically developing kindergarten children aged 3–5 years. Children aged 6 years will be excluded to avoid attrition due to their transition to primary school. The inclusion criteria are as follows: (1) Participants must be aged between 3 and 5 years (preschoolers). (2) Participants must attend a kindergarten in each of the 18 administrative districts in Hong Kong. (3) Participants must be free of any illness or disability that might interfere with their ability to complete the FMS, physical activity, daily tasks, or cognitive tasks required for the intervention. (4) Prior to enrollment in the intervention, informed consent signed by a parent or guardian must be obtained. The exclusion criteria are as follows: (1) Participants out of the age range of 3–5 years. (2) Participants who cannot attend kindergarten regularly. (3) Participants with known medical conditions or disabilities that would limit their participation in completing the FMS, physical activity, daily tasks, or cognitive tasks required for the study intervention and assessments. (4) Participants who did not provide consent from their parents or guardian.

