### Data collection procedures

Data collection will follow a cyclical pattern: 1-week pre-test, 3-week intervention, 1-week post-test, and 6-week washout. This cycle will be repeated three times, followed by a final post-test at week 38 and three follow-up tests at 8-week intervals (weeks 46, 54, and 62). See Table 1 for the detailed schedule. In the CRXO design of this study, from the cohort perspective, each cluster is required to receive all 4 interventions sequentially; from the cross-sectional perspective, each cluster is required to receive 4 different interventions each at the same time; thus, a total of 24 combinations of the intervention sequence are generated (4*3*2). Since the effect of the intervention sequence on the results of the study will not be considered, this study will use GraphPad Software to randomly select the combination of the intervention sequence to be used in the study.

**Table 1 Tab1:** Schedule of the cluster randomized crossover trial

Schedule of Interventions 2025–2026		
20/10/2025-26/10/2025	1 week	Pre-test 1
27/10–16/11	3 weeks	Intervention 1
17/11–23/11	1 week	Post-test 1
24/11/2025-4/1/2026	6 weeks (Including Public Holiday for Christmas)	Washout period 1
5/1–11/1	1 week	Pre-test 2
12/1–1/2	3 weeks	Intervention 2
2/2–8/2	1 week	Post-test 2
9/2–22/3	6 weeks (Including Public Holiday for Spring Festival)	Washout period 2
23/3–29/3	1 week	Pre-test 3
30/3–19/4	3 weeks	Intervention 3
20/4–26/4	1 week	Post-test 3
27/4–7/6	6 weeks	Washout period 3
8/6–14/6	1 week	Pre-test 4
15/6 − 5/7	3 weeks	Intervention 4
6/7–12/7	1 week	Post-test 4
13/7 − 6/9	8 weeks (13/7–31/8 for washout, 1/9 − 6/9 for test)	Follow-up 1
7/9 − 1/11	8 weeks (7/9–25/10 for washout, 26/10 − 1/11 for test)	Follow-up 2
2/11–24/12	8 weeks (2/11–17/12 for washout, 18/12–24/12 for test)	Follow-up 3

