**Fig. 2 Fig2:**
[figure not shown]
Timeline of enrollment, interventions, and assessments of the “AMPLE” program. ^a ^In each 3-week intervention period, clusters receive one of four conditions: (1) FMS with cognitive challenge, (2) Sedentary with cognitive challenge, (3) FMS without cognitive challenge, or (4) Sedentary without cognitive challenge. As this is a cluster randomized crossover trial, each cluster receives all four conditions sequentially over the course of the study. ^b ^Arrow indicates continuous delivery of intervention.^c^ Implementation Fidelity includes workshops, logs, questionnaires and interviews for teachers.*Abbreviations*: *20mSRT*-*PREFIT* 20 m Shuttle-Run Test PREschoolers FITness Assessment, *Borg CR*-*10 * Borg Category-Ratio 10 Scale, *EmQue* Empathy Questionnaire, *FMS* Fundamental Movement Skills, *SCBE*-*30* Social Competence and Behavior Evaluation Scale, *SST* Stability Skill Test, *TGMD*-*3* Test of Gross Motor Development, Third Edition, *TRAILS*-*P *Trial Making Test for Preschoolers, *WLR * Word List Recall Test

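### H1-H5 are carried into follow-up, but by weeks 46, 54 and 62 every class has had all four conditions, so no follow-up contrast is free of earlier exposure

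*Protocol article*

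**What the plan says.** The Background sets the time frame for all five hypotheses with the words "We hypothesize the following after the intervention and follow-up". Each one then predicts an advantage over a concurrent group. H2, for example, expects "greater increases in executive function than their counterparts in the control group", with the combination group improving most.

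The Abstract gives the purpose of the later tests: "Three follow-up tests will be conducted within six months after the end of the intervention to evaluate the long-term impact of the program".

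The design sections describe a full crossover. Data collection procedures says that "each cluster is required to receive all 4 interventions sequentially", and the Fig. 2 legend repeats that "each cluster receives all four conditions sequentially over the course of the study". Study design says the same, and Strengths and potential limitations describes each class as its own control. Table 1 places Follow-ups 1, 2 and 3 after Post-test 4. No class is described as held back or untreated.

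Three further statements bear on the point. Data collection procedures says the effect of sequence will not be considered. Data analysis names intervention days and group as fixed effects, with their interaction, and gives no rule for which group a class belongs to at follow-up. Strengths and potential limitations admits that no evidence establishes the best washout length, and it expects losses at follow-up. It does not mention the missing comparator.

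**The concern.** A between-condition hypothesis needs classes that differ in exposure to the conditions being compared. Within a period they do, because at each post-test some classes have just finished the combination condition and others the control. After period 4 they do not, because total exposure is the same everywhere. The follow-up part of H1-H5 therefore refers to control-group counterparts who have also had the combination, cognitive and physical conditions.

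Without that comparator, change between week 38 and week 62 mixes three things: ordinary development, which the Washout period section itself calls rapid at this age; practice from repeated testing; and whatever the programme left behind. If this change were reported against H1-H5, a long-term effect could be claimed that the data cannot attribute to any condition. The Discussion intends to carry the findings into education and public-health policy, so the claim would matter.

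**Working it through.** **Inputs.** Dates come from Table 1, the follow-up weeks and the crossover rule from Data collection procedures, and the hypotheses from the Background. I read the cluster that moves through the conditions as the class, in line with the Abstract and Strengths and potential limitations.

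**1. The protocol's own weeks.** Week = whole weeks since 20/10/2025, plus 1.
- Post-test 4 starts 6/7/2026: 259 days, 259/7 = 37.0, week 38.
- Follow-up 1 starts 1/9/2026: 316/7 = 45.1, week 46.
- Follow-up 2 starts 26/10/2026: 371/7 = 53.0, week 54.
- Follow-up 3 runs 18/12 to 24/12/2026: 424/7 = 60.6 and 430/7 = 61.4, weeks 61-62.

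These agree with the stated 38, 46, 54 and 62.

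**2. Weeks from the end of each intervention period to each follow-up test.** The periods end on 16/11/2025, 1/2/2026, 19/4/2026 and 5/7/2026.

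| Test | Period 1 | Period 2 | Period 3 | Period 4 |
|---|---|---|---|---|
| Follow-up 1 | 41.3 | 30.3 | 19.3 | 8.3 |
| Follow-up 2 | 49.1 | 38.1 | 27.1 | 16.1 |
| Follow-up 3 | 56.7 | 45.7 | 34.7 | 23.7 |

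Each class has one condition in each column. Classes differ only in which condition sits where.

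**3. Is combination minus control estimable?** This was checked by the rank of the design matrix over all 24 orders.
- Within-period post-tests, period plus condition: estimable.
- Follow-up, exposure to each condition as the predictor: all 24 rows are identical, rank 1, not estimable.
- Follow-up, a separate effect for each condition in each position: rank 10 of 17 columns. The last-position contrast is not estimable; only differences between positions are.
- Follow-up, last condition only: estimable, because the effects of the three earlier conditions are set to zero.

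**4. What the last-condition contrast measures if that zero is wrong.** Take two classes at Follow-up 1 with the same first two conditions. Class A had control in period 3 and combination in period 4; class B had the reverse. Let e(c, t) be what remains of condition c after t weeks, and assume that residual effects add. Then

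A − B = [e(comb, 8.3) − e(comb, 19.3)] − [e(control, 8.3) − e(control, 19.3)].

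With control as the zero reference this is e(comb, 8.3) − e(comb, 19.3). An effect that lasts undiminished gives zero. The contrast measures how recent the exposure was, and a durable benefit is exactly what it would miss.

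**5. Where retention can be estimated.** Intervention 1 ends 16/11/2025 and Pre-test 2 starts 5/1/2026: 14 + 31 + 5 = 50 days, or 7.1 weeks. At that point each class has had one condition, and the four classes in a kindergarten have had different ones. With 18 kindergartens that is 18 × 4 = 72 classes, 18 per condition, compared as a randomised parallel design. By Pre-tests 3 and 4 the classes have had two and three conditions, so those comparisons need a carry-over assumption. Period 4 has no following pre-test.

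**The case against.** The strongest reply is that the document writes no between-condition test at follow-up. The Abstract speaks of the programme's impact, which a description of trajectories could meet. Data analysis bases the effect size on post-intervention means, and a follow-up estimand could sit in an analysis plan not shown here. The first part stands: the problem enters through the hypothesis statement and the stated follow-up purpose, not through a specified model. But an analysis plan can choose a model; it cannot supply classes that were never exposed.

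A reader might infer something stronger: that no randomised contrast of any kind exists at follow-up and nothing can be estimated. The documents do not support that. Sequences are randomly selected and the conditions run side by side, so classes differ by design in their last condition. That contrast is valid if earlier conditions leave no residue, and the crossover already relies on a related assumption through its washout. The difficulty is one of plausibility. If effects are gone by the next pre-test at 7.1 weeks, little should remain at 8.3 to 23.7 weeks. If they last that long, earlier conditions enter the contrast.

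A reader might also infer that the follow-up sample is selected by age, since the Participants section says that "Children aged 6 years will be excluded to avoid attrition due to their transition to primary school". That is an entry criterion, and it removes nobody who turns 6 later. The article gives neither the share of children aged 5 at entry nor a school-entry date, and it already expects follow-up losses. Age selection is not shown and forms no part of this point.

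**Conclusion.** The point holds in this form: H1-H5 reach into follow-up, where no contrast is free of earlier exposure. It affects 3 of the 11 test occasions (4 pre-tests, 4 post-tests, 3 follow-ups), the follow-up part of all five hypotheses, and the long-term purpose stated in the Abstract. The within-period post-test comparisons, which carry the crossover, are not affected by this problem.

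The conclusion rests on every class completing all four periods as planned and on no class being held back. It does not depend on sample size, effect size or dropout. The algebra for the last-condition contrast also assumes that residual effects add.

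A separate and minor labelling point lies in the same section. Research question (a) asks for effects "compared with usual care", but no arm is described that way. The comparator in Intervention strategy is a 30-minute seated story session designed for minimal cognitive engagement. H1-H5 themselves refer correctly to the control group.

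**What to change.** 1. Reword the lead-in to H1-H5 so that the hypotheses apply to the post-test of each period. Describe weeks 46, 54 and 62, here and in the Abstract, as uncontrolled follow-up of children who have had all four conditions, with no between-condition test and no long-term efficacy claim.
2. Name Pre-test 2 as the randomised retention comparison between conditions. The same contrast shows whether differences survive the first washout. If Pre-tests 3 and 4 are also used, state the carry-over assumption.
3. In research question (a) and in later conclusions, name the sedentary story-time control as the comparator.

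The cost is rewording and one added analysis of data already scheduled. What is lost is the controlled six-month claim. The replacement reaches only about 7 weeks, and it compares different classes within one period, so it lacks the gain from each class serving as its own control.

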
## Methods

### Study design

This study follows the 2025 Standard Protocol Items: Recommendations for Interventional Trials (SPIRIT) guidelines [37] and will evaluate the effectiveness of the “Advancing Movement and Physical Literacy Earlier” (AMPLE) program, a novel intervention designed to promote physical literacy and physical activity among young children in Hong Kong. The study will employ a four-arm cluster randomized crossover (CRXO) trial design, an approach particularly well-suited for interventions delivered within established settings like kindergartens [38]. The CRXO design offers the advantage of controlling for potential cluster-level confounders and allows each participating cluster to experience all intervention conditions, thereby increasing statistical power [39, 40].

### Randomization

According to the Hong Kong Education Bureau, there are 1,026 kindergartens in Hong Kong in 2022–2023 in 18 districts in 3 regions of Hong Kong Island, Kowloon, and the New Territories [41]. In this study, one kindergarten will be randomly selected from each district, and an email and invitation letter will be sent to the kindergarten principals through a computer-generated randomized sequential list (GraphPad Software, Inc.). After the principals agreed to participate, a randomized sequential list will be generated in the same manner for each kindergarten class, and the four participating classes will be finalized. Then a series of documents related to the intervention, including the theoretical background, the study objectives, the research methodology, and the timeline will be sent to the relevant administrators and teachers of the kindergartens. The parents or guardians of the children participating in the intervention will receive documents including ethics approval from qualified institutions, consent forms, research objectives, timetables, etc., and must sign the consent form before the child can be included as a participant in the study.

